### Outcomes

The following will data will be analysed to address the primary (feasibility) objectives of the trial:

#### Recruitment, randomisation and retention

Number of participants screened, eligible and successfully recruited into the trial, along with characteristics of non-consenting and ineligible participants.Total number of participants enrolled in the allocated recruitment period and time to complete recruitment in each country.Retention of trial participants in their original trial arms following randomisation and the proportion of participants attending data collection follow-ups at 6, 12 and 26 weeks along with number and reasons for dropping out.

#### Intervention delivery

The proportion of participants attending the pre-quit and post-quit sessions, the number of quit and post-quit sessions conducted per participant.The proportion of trial participants receiving low (4mg) vs high (6mg) dose NRT, the proportion of participants retaining their medication charts and demonstrating their adherence to NRT at follow-up visits.

#### Data collection methods

Proportion of completed baseline and follow-up assessments in each armTotal number of participants eligible to provide saliva samples at 12 and 26 weeks and number of trial participants successfully providing a saliva sample.

The following data will be collected and analysed to address part of the secondary objectives, i.e. the identification of cessation outcomes for the main trial:A 7-day point prevalence of tobacco use (smoked and smokeless) at 6 weeks, 12 weeks and 26 weeks of follow-ups. At 26 weeks, the point prevalence will be verified by CO breath test (<10ppm) and salivary cotinine assessment (<15ng/ml).Continuous abstinence to all forms of tobacco at 26 weeks post-quit date. This will be self-reported only, as we did not attempt to validate abstinence every week.

Other aspects of the secondary objectives such as process evaluation and health economic procedures are described in subsequent sections.

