**Methods:**

We will conduct a factorial design, randomised-controlled pilot trial in Bangladesh, India and Pakistan. Daily ST users will be recruited from primary health care settings in Dhaka, Noida and Karachi. Participants will be individually randomised to receive intervention A (4 or 6 mg NRT chewing gum for 8-weeks), intervention B (BISCA: face-to-face behavioural support for ST cessation), a combination of interventions A and B or usual care (Very Brief Advice - VBA). The participants will provide demographic and ST use related data at baseline, and at 6, 12 and 26 weeks of follow-up. Salivary cotinine samples will be collected at baseline and 26 weeks. The analyses will undertake an assessment of the feasibility of recruitment, randomisation, data collection and participant retention, as well as the feasibility of intervention delivery. We will also identify potential cessation outcomes to inform the main trial, understand the implementation, context and mechanisms of impact through a process evaluation and, thirdly, establish health resource use and impact on the quality of life through health economic data.

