Saliva samples for biochemical verification of tobacco abstinence will be collected from all participants at baseline and those self-reporting abstinence to all forms of tobacco at 12 and 26-week follow-ups. Self-reported continued NRT use at these follow-ups will delay the collection of a saliva sample until participants report its use as discontinued. A CO breath test will also be administered at these time points to these participants to rule out any smoked tobacco use. The saliva samples from Bangladesh and Pakistan will be transferred to a specialist laboratory (ABS laboratories, York, UK) for biochemical analysis for salivary cotinine while those collected in India will be analysed locally through an accredited laboratory.

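### Continuous abstinence at 26 weeks rests on self-report alone, so a participant can fail the 26-week CO or cotinine check and still count as continuously abstinent

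*Protocol article*

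**What the plan says.** Under Outcomes, Data collection methods, the article lists two cessation measures that serve the secondary objective of choosing outcomes for the main trial.

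- Point prevalence: "A 7-day point prevalence of tobacco use (smoked and smokeless) at 6 weeks, 12 weeks and 26 weeks of follow-ups". Verification is written in for the last visit only: "At 26 weeks, the point prevalence will be verified by CO breath test (<10ppm) and salivary cotinine assessment (<15ng/ml").
- Continuous abstinence: "Continuous abstinence to all forms of tobacco at 26 weeks post-quit date", followed by "This will be self-reported only, as we did not attempt to validate abstinence every week".

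Data collection and follow-up procedure describes the samples. Saliva for biochemical verification is "collected from all participants at baseline and those self-reporting abstinence to all forms of tobacco at 12 and 26-week follow-ups". CO is taken alongside: "A CO breath test will also be administered at these time points to these participants to rule out any smoked tobacco use". Saliva is postponed for anyone who reports still using NRT. Table 2 marks cotinine and CO at 12 and 26 weeks. The feasibility outcomes also count how many participants are eligible for, and give, saliva at both visits. The abstract's Methods paragraph leaves out week 12: "Salivary cotinine samples will be collected at baseline and 26 weeks".

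**The concern.** The two 26-week measures should be nested. Someone who has used no tobacco since the quit date has used none in the last seven days, so continuous abstainers should be a subset of point-prevalence abstainers. Attaching the biochemical check only to the looser measure breaks this, and the stricter measure could even show more successes than the looser one.

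The setting makes self-report a weak basis. Allocation is open. BISCA schedules one pre-quit, one quit and six post-quit sessions (1 + 1 + 6 = 8), while usual care is about 1 to 1.5 minutes of advice with no further advisor contact. Over-reporting that differs by arm is therefore plausible. The Statistical analysis section will produce risk ratios with 95% intervals for these outcomes, and the pilot is meant to inform which of them the main trial adopts.

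**Working it through.** **Is the test available for everyone who needs it?** A participant who claims continuous abstinence to 26 weeks necessarily reports abstinence at the 26-week visit. Those are the people from whom saliva and CO are taken. Apart from delayed or missing samples, every claim of continuous abstinence comes with a scheduled test.

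**What happens to a failed test?** Take a participant who reports no tobacco since the quit date and has cotinine of 15 ng/ml or more, or CO of 10 ppm or more, at 26 weeks.

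| Outcome at 26 weeks | Rule in the article | Classification |
|---|---|---|
| 7-day point prevalence | self-report, CO and cotinine | not abstinent |
| Continuous abstinence | self-report only | abstinent |

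This assumes that continuous abstinence means no use, as the article's wording has it; no allowance for lapses is stated.

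**Does the stated reason cover it?** Without weekly tests, abstinence between visits cannot be confirmed. Contradicting a claim needs only one valid failed test. The reason supports saying that the period is not fully verified; it does not support disregarding the 26-week result.

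**Plan figures.** Nothing in the sample size depends on how abstinence is ascertained. It reproduces: ln(0.05)/ln(0.95) = 58.4, so 59, against a stated minimum of 60 per country; 80 × 1.10 = 88; 3 × 88 = 264; 264/4 = 66 per arm.

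**Possible size (all rates assumed, since the documents give none).** Let self-reported continuous abstinence be 10% in control and 20% in an active arm (risk ratio 2.0, risk difference 10 points), with 66 per arm. Let f be the share of claims that fail verification; verified rate = self-reported rate × (1 − f).

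| f control | f active | Verified rates | Risk ratio | Risk difference |
|---|---|---|---|---|
| 0% | 0% | 10% vs 20% | 2.0 | 10 points |
| 20% | 20% | 8% vs 16% | 2.0 | 8 points |
| 40% | 40% | 6% vs 12% | 2.0 | 6 points |
| 20% | 40% | 8% vs 12% | 1.5 | 4 points |
| 40% | 20% | 6% vs 16% | 2.67 | 10 points |

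Participants affected: control 66 × 0.10 × 0.40 = 2.6 at most; active 66 × 0.20 × 0.40 = 5.3 at most.

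A second illustration assumes no true effect: 10% truly abstinent in both arms, and false claims by 2% of continuing users in control against 5% to 10% in BISCA. The self-reported risk ratio is (0.10 + 0.90 × 0.05)/(0.10 + 0.90 × 0.02) = 0.145/0.118 = 1.23, rising to 0.190/0.118 = 1.61.

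**Against sampling error.** For 10% versus 20% with 66 per arm, the standard error of the log risk ratio is √(0.9/6.6 + 0.8/13.2) = √0.197 = 0.444. The 95% interval is 2.0 × exp(±0.870), or 0.84 to 4.8, which is wider than any shift in the table.

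**The case against.** The self-report rule is disclosed and a reason is given. A fully verified measure stands beside it at the same visit, both are candidates only, and any discordance would show once both are reported. Cessation is secondary to feasibility, the Statistical analysis section rules out inference, and the Discussion concedes that the sample is too small to judge effectiveness. All of this stands and lowers the severity. It does not remove the conflict between two definitions at one visit.

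Four stronger readings are tempting and not supported:

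- *A reader might infer that 12-week abstinence goes unverified and that those samples serve no purpose.* The follow-up section takes them for verification, and they feed a feasibility count. The outcome definition simply does not mention them, which is a wording gap.
- *A reader might infer that any raised cotinine proves tobacco use.* The article delays saliva during reported NRT use, so it recognises that NRT undermines the test, and unreported NRT could produce a failure without tobacco. NRT is supplied in two of the four arms, and cessation products bought over the counter are expected among the costs. The article already accepts this limit for 26-week point prevalence.
- *A reader might infer that any failed 12-week test should cancel continuous abstinence.* Samples delayed by NRT no longer describe the 12-week visit, and delay is likelier in the NRT arms, so a strict rule could itself classify by arm.
- *A reader might infer that self-report inflates BISCA's effect.* Table 2 gives follow-up CRFs, saliva and CO to research staff, not advisors, and post-quit sessions stop after lapses in two consecutive weeks. Differential over-reporting is plausible; its direction is not shown.

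**Conclusion.** The point holds for the 26-week definition. The article has a test result for those claiming continuous abstinence, uses it for one outcome and ignores it for the stricter one, on a ground that does not justify doing so. That follows from the text and needs no assumed rate.

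Severity is moderate. No stated figure changes, the outcome is secondary, and no inference is planned. Under the assumed rates, at most about 3 control and 5 active participants per 66 are affected, and the risk ratio may fall, rise or stay put depending on how failure divides between arms. The documents establish neither size nor direction. The consequence that matters is for the main trial, which could inherit a strict-sounding outcome with the weaker measurement.

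**What to change.** In the cessation outcomes under Data collection methods:

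1. Define continuous abstinence at 26 weeks as self-reported abstinence since the quit date plus CO <10 ppm and cotinine <15 ng/ml at 26 weeks. Use the thresholds already set for point prevalence, and treat NRT-delayed or missing samples in the same way as for that outcome.
2. Keep the self-report version as a sensitivity analysis, so that the pilot shows how often self-report fails verification.
3. Where a valid off-NRT sample exists at 12 weeks, use it to verify 12-week point prevalence and report it as supporting evidence for continuous abstinence, not as an automatic disqualifier.
4. Reconcile the saliva schedule in the abstract (baseline and 26 weeks) with the follow-up section, Table 2 and the outcomes (12 weeks as well).

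No extra visit, sample or assay is needed, because the tests are already scheduled. The costs are revised wording, a somewhat lower reported rate, and some possible misclassification from unreported NRT use.

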### Sample size

We calculated the sample size in line with recommendations by Viechtbauer et al. [29], which state that the sample size should be sufficiently large to capture at least one incidence of a range of anticipated and unanticipated outcome events. Assuming the probability of these outcome events to lie between 5 and 10%, we estimated at least 60 participants in each country, using a confidence level of 95%. We increased this number to 80 participants per country in order to have at least 20 participants per trial arm and further inflated this figure by 10% to account for potential loss to follow-up. In total, we thus require 88 participants per country (22/trial arm) with a combined total of 264 participants in Bangladesh, India and Pakistan.

### Statistical analysis

Descriptive data analyses will be performed to describe participant characteristics, as well as to address the feasibility objectives identified above. Reporting will be done for the overall sample and where relevant, stratified for each country. Measures will include summary statistics such as mean and standard deviation for continuous variables and frequencies (absolute and relative) for categorical variables. We will estimate risk ratios and 95% confidence intervals for the potential cessation-related outcomes as a preliminary assessment of effect. No inferences however will be made based on these results. All statistical analysis will be performed on STATA version 16 [30].

### Process evaluation

The process evaluation will be informed by the Medical Research Council guidance [31]. This identifies three components: implementation, mechanisms of impact and context.

#### Implementation and context

One to 2 cessation advisors will be interviewed in each country to explore their experiences of delivering the BISCA and NRT interventions. The impact of factors such as the community environment and other social, economic, cultural, environmental and political factors will be assessed. Fidelity to delivering the BISCA/NRT interventions will be assessed using a fidelity index adapted from the original BISCA study [18]. This will be applied to audio-recordings of nine randomly selected participants per country (3 per intervention arm, excluding those allocated to receive VBA) who have completed their allocated intervention.

#### Mechanisms of impact

All participants will complete a short questionnaire at 6-week follow-up which will have some acceptability questions on trial processes. The questionnaire will also explore the engagement with BISCA and NRT intervention components, acceptability of the sessions and perceived benefits/dis-benefits. A purposive sample of 24 participants in each country (8 from each intervention trial arm), a mix of men and women who have/have not quit ST will be interviewed to explore key issues that emerged in the questionnaire. Data on potential mediators (see Fig. 1) will be collected at all time points.

Interviews will be conducted using a topic guide and digitally audio-recorded. The quantitative data from the fidelity index and questionnaire will be analysed using descriptive statistics. The qualitative data from the questionnaire will be analysed using content analysis [32], while transcribed and translated interviews will be analysed using the Framework Approach [33]. Micorosoft Excel will aid data handling. The integration of interview findings with respective questionnaire data will be done using a ‘triangulation protocol’ [34].

### Health economics

The analysis of economic data will include a preliminary assessment of the costs associated with implementing BISCA (alone or in combination with NRT) and NRT alone as well as a change in EQ-5D-3L scores between the baseline and 26 weeks post-baseline. The overall assessment will include a commentary on the suitability/feasibility of an economic evaluation alongside a future definitive trial.

### Data management

Each country site will hold data in accordance with both the UK (General Data Protection Regulation [35], Data Protection Act 2018 [36] and any additional country-specific requirements. Collected data will be identified by a unique identification number (i.e. the Trial ID number) only. Study files will be stored in accordance with UK Good Clinical Practice (GCP) guidelines [37]. The collected data will be stored separately from the consent sheets to maintain the anonymity of data. Research staff at the University of York will develop and maintain an electronic database that will be used to enter data by research staff in each participant country. The database will be uploaded to a secure server provided by York University IT services and accessible only to researchers directly involved in the study or by representatives of the Trial Data Management and Ethics Committee in the event of a study audit. Similarly, all audio files and anonymised transcripts will be uploaded and kept secure throughout the duration of the study. Paper versions of study documents at the participating sites, the country coordinating centers and the University of York will be retained in a secure (locked when not in use) location, during and after the trial has finished. All essential documents, including source documents, will be retained for a minimum period of 5 years after study completion.

### Trial monitoring procedures

Mechanisms for trial monitoring include collection and reporting of adverse events, regular trial audits and safety monitoring by an independent Data Management and Ethics Committee (DMEC).

#### Adverse events

A standardised approach for adverse events will be followed for their identification, recording and reporting. Checklists will be completed each week, either face-to-face or via a phone call, to assess the frequency and severity of Adverse (AEs) and Severe Adverse Events (SAEs). All participants will also have access to a central number to report any sudden onset AEs. Reported AEs will be assessed by the country trial coordinator for seriousness, severity and relatedness to the intervention. AEs related to the intervention will also be assessed for their expectedness. Those with the potential to become SAEs will be monitored till resolution. SAEs which are related to the intervention will be reported to the DMEC and Trial Steering committee within 3 days and the local Ethics Committees within 15 days. The participants who experience serious unexpected AEs related to the intervention will be withdrawn from treatment but will continue to be followed up in their respective trial arm.

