### Details of interventions

As described above, the trial participants will receive Nicotine replacement therapy (Intervention A) or BISCA (Intervention B), either alone or in combination. The participants not randomised to receive these interventions will receive usual care in the form of VBA [24] offered by a trained cessation advisor. The VBA will last approximately 1–1.5 min. It incorporates the 3As approach (Ask, Advise, Act) previously used for delivering smoking cessation in healthcare settings [24]. During this brief interaction, the advisor will (i) ask about the type of ST product consumed, (ii) identify ST related harms and advise on stopping its use and (iii) act by providing a self-help leaflet to prompt quit planning. Participants receiving VBA will have no further interactions with the cessation advisor. VBA will also be offered to other ST using individuals who are either ineligible for trial participation or those who do not provide informed consent. Details of interventions A and B are provided in further detail below:

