#### Intervention A: Nicotine replacement therapy

NRT will be provided to trial participants alongside VBA and the self-help leaflet (described above). Following randomisation, the participants will undertake an 8-week course of NRT chewing gum (Nicorette or its generic equivalent, as per availability in each country); they will receive either 4mg or 6 mg NRT supplies depending on their baseline assessment. A cessation advisor will assess each participant’s tobacco use through two items of the heaviness of Tobacco Use Index [25]: (i) time to first ST use and (ii) average number of daily ST intakes (chews/dips). All participants will receive a standard 4mg dose; however, those who report their first ST intake within 30 min of waking, or consuming ST >10 times/day) will receive a 6-mg dose. The 6-mg dose will be given as a combination of 4-mg and 2-mg nicotine chewing gums taken together.

NRT will be provided by the cessation advisor at the time of recruitment. The participants will be instructed to start using NRT on an hourly basis, up to 15 doses in a day starting from their planned quit date. The first dose will be taken within the hour of waking or as soon as craving develops. They will be instructed to perform the ‘park and chew’ method [26], which involves chewing the gum until a peppery or flavoured taste emerges, ‘parking’ it between cheek and gum to facilitate nicotine absorption through the oral mucosa for approximately 30 min or until taste dissipates. A leaflet providing this information in written form will also be provided.

All participants will be provided with an initial 2-week NRT supply following randomisation; subsequent two weekly supplies of NRT will be provided by a trained research officer to participants who report and demonstrate consumption of NRT on at least 5 days in the previous week. Any adjustments to participants’ NRT dosing, if necessary, will be made in light of participants’ experiences in the first week of its use. Where available, participants will be provided the option to choose alternate NRT flavours in order to maximise their adherence to treatment.

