**Fig. 1 Fig1:**
[figure not shown]
The BISCA logic model identifying potential mechanisms of action (MoAs) and their underlying behaviour change techniques (BCTs)—MoAs are identified in bold text in each box, with related BCTs listed underneath

The participants receiving BISCA will be scheduled for an initial (pre-quit) contact session on the day of randomisation or on another convenient day in the same week. Activities delivered in this session focus on building knowledge around the ST ingredients and harms related to ST use, building self-efficacy and preparing participants for making a quit attempt. The participants will receive one pre-quit session prior to the quit date; however, those who are unable to proceed with a quit attempt will be eligible to receive an additional pre-quit session.

The quit session will be scheduled in the week of the participants’ quit date (either on the same day or 2–3 days preceding the quit date). Each participant will receive one quit session which will focus on strengthening their ex-user identity, identifying triggers and withdrawal symptoms and discussing strategies to manage these. They will also be provided with a self-help calendar on this day for monitoring progress and setting self-incentives.

After the quit session, the participants will receive six weekly post-quit sessions with their cessation advisor. These sessions will focus on the reinforcement of key messages delivered in pre-quit and quit sessions, as well as support in avoiding relapse and minimising withdrawal effects.

The pre-quit session will be conducted at the recruitment centres, while the quit and post-quit sessions will either be delivered at the same place or in participants’ homes. The sessions will be scheduled in advance, and a reminder will be issued to participants ahead of the visit. Those who are unable to attend or have to cancel their scheduled visit will be rescheduled on a convenient date within the same week. A log of delivered sessions will be maintained by the advisors to record the total number of contacts made with each participant. The participants who report lapses on two consecutive weeks will receive no further post-quit sessions; however, they will be provided VBA to plan and execute their next quit attempt. The participants who are non-responsive to phone calls or home visits on three separate occasions will be considered as being lost to follow-up and continuing their ST use.

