### Data collection and follow-up procedure

After recruitment, enrolled trial participants will complete an interviewer-administered Case Report Form (CRF) at baseline. Collected data will include participants’ socio-demographic and household information, current tobacco use, mood and physical symptoms, nicotine dependence, contact with health providers, attempts to quit ST, motivation to quit ST and mediators of ST cessation. These assessments will also be repeated at 6, 12 and 26 weeks following their quit date (Table 2).

**Table 2 Tab2:** Schedule of research activities

Activity/assessment	***Stage of study***								
	Study member	Recruitment		Intervention			Follow-up		
		Pre-enrolment	Post-enrolment	Pre-quit	Quit	Post-quit	6 weeks	12 weeks	26 weeks
		Screening & consent	Baseline /randomisation	Pre-quit session(s) (BISCA)	Quit session (BISCA)	6 Weekly BISCA sessions	Follow-up 1	Follow-up 2	Follow-up 3
Screening log	Research staff	X							
Eligibility form	Research staff	X							
Informed consent	Research staff	X							
Random allocation	Research staff		X						
Baseline CRF	Research staff		X						
Health resource use Questionnaire	Research staff		X						X
Quality of life assessment (EQ-5D-5L)	Research staff		X						X
VBA for ST cessation	Advisor		X						
BISCA sessions	Advisor			X	X	X			
Adverse/serious adverse events checklist	Research staff/advisor				X	X	X	X	
Follow up CRF	Research staff						X	X	X
Salivary cotinine (biochemical verification)	Research staff		X					X	X
CO assessment	Research staff	X	X					X	X
Qualitative interviews for process evaluation	Research staff						X		

*BISCA* behavioural support intervention for smokeless tobacco cessation in adults, *CRF* case-report forms, *CO* carbon monoxide, *ST* smokeless tobacco, *VBA* very brief advice

Health resource utilization and quality of life (using the EQ-5D-3L instrument [28]) will be measured at baseline and 26-week follow-up as part of a preliminary economic assessment. Taking healthcare provider and patient perspectives, health resource use will include the costs of delivering the specified intervention in each arm (including staff time, materials and logistics), any health service use (including visits to a healthcare provider, primary or tertiary care facility) and any out-of-pocket costs (including travel costs, fees paid to healthcare providers and costs of medicines including any smoking cessation pharmacotherapy bought over-the-counter).

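### The adverse-event text requires weekly checks with no stated end, but Table 2 schedules only one check after week 6 and ties the earlier checks to columns headed as BISCA sessions

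*Protocol article*

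**What the plan says.** - **Protocol article, Adverse events.** "Checklists will be completed each week, either face-to-face or via a phone call". The sentence gives no end date and no limit by arm. The section also gives every participant a central number for reporting sudden-onset events.
- **Protocol article, Data collection and follow-up procedure, Table 2.** The row "Adverse/serious adverse events checklist" is assigned to research staff or advisor. It is marked in the Quit column (sub-headed as a BISCA session), the Post-quit column (sub-headed "6 Weekly BISCA sessions"), and at weeks 6 and 12. It is blank at week 26.
- **Protocol article, Intervention B: BISCA.** "After the quit session, the participants will receive six weekly post-quit sessions with their cessation advisor". These sessions can end early: "The participants who report lapses on two consecutive weeks will receive no further post-quit sessions". Under Table 1, only arms 3 and 4 receive BISCA.
- **Protocol article, Details of interventions.** "Participants receiving VBA will have no further interactions with the cessation advisor".
- **Protocol article, Intervention A.** The gum course lasts 8 weeks from the planned quit date, and after the first supply "subsequent two weekly supplies of NRT will be provided by a trained research officer", conditional on demonstrated use. Table 2 attaches no AE check to these resupply contacts.

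**The concern.** The article gives two AE schedules that cannot both be followed. Staff in three countries have to choose between them, and the choice affects how actively events are sought while participants are still using NRT.

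There is also a risk to comparability. The columns carrying the early AE marks are labelled as sessions that arms 1 and 2 never attend. If a site works from Table 2, participants in the BISCA arms are asked about events most weeks, while NRT-only and usual-care participants are first asked at week 6. Differences in AE counts between arms could then arise from questioning alone. If checks also lapsed when BISCA sessions stop, questioning within arms 3-4 would depend on whether the participant had relapsed.

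The DMEC is asked to assess safety and may recommend stopping or modifying an arm (Data monitoring and ethics). It would be reading counts whose meaning depends on which schedule was used.

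**Working it through.** The plan gives no figure of its own for the number of AE checks, so the check is a count of scheduled contacts followed by an illustration.

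**Step 1. Scheduled AE checks per participant, weeks counted from the quit date**

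| Source and reading | Arms 3-4 | Arms 1-2 |
|---|---|---|
| Text, weekly, to week 12 | 12 | 12 |
| Text, weekly, if carried to week 26 | 26 | 26 |
| Table 2, columns read literally as BISCA sessions | 1 + 6 + 2 = 9 (8 if the sixth session coincides with the week-6 visit) | 2 |
| Table 2, columns read as calendar stages, arms 1-2 checked by phone | 8-9 | 8-9 |

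**Step 2. The conflict that does not depend on how the columns are read.** From week 7 to week 12 the text implies 6 checks. Table 2 has 1, at week 12, in every arm. The five weeks without a check (7 to 11) include weeks 7 and 8 of the NRT course. After week 12 the table has none, while the text sets no end.

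**Step 3. The conflict that does depend on it.** Under the literal reading the arms differ by 8 - 2 = 6 or 9 - 2 = 7 scheduled checks. If AE checks also ended with the sessions, a BISCA participant reporting lapses at the first two weekly sessions would have 1 + 2 + 2 = 5. Under the calendar-stage reading the difference between arms is zero.

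**Step 4. Illustration of the literal reading.** Assume the same true weekly AE risk *h* in all arms, and that an event is recorded only if a check falls in the week it occurs (no recall at later visits, no use of the central number). With *k* checks, P(at least one AE recorded) = 1 - (1 - *h*)^*k*. The article gives no AE rate; *h* = 2% and 5% are assumptions.

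| *h* | *k* = 9 | *k* = 8 | *k* = 2 |
|---|---|---|---|
| 5% | 1 - 0.95^9 = 0.370 | 1 - 0.95^8 = 0.337 | 1 - 0.95^2 = 0.098 |
| 2% | 1 - 0.98^9 = 0.166 | 1 - 0.98^8 = 0.149 | 1 - 0.98^2 = 0.040 |

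The contrast is therefore at most about 15-37% against 4-10%.

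**The case against.** The strongest reply is that the difference between arms is inferred and nowhere stated. The top-level headings of the two columns are the stages Quit and Post-quit, with BISCA only in the sub-headers. The row for BISCA sessions names the advisor alone, whereas the AE row also names research staff. The text describes a standardised approach and allows phone contact, which is what arms without sessions would need. Usual-care participants have no further contact with the advisor, but nothing bars calls from research staff. Lapses end BISCA sessions, but nothing says they end AE checks. All of this stands.

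A reader might infer that the plan builds in biased ascertainment, so that NRT-only would be under-recorded and BISCA would look harmful. The document does not support that. It leaves room for such an outcome and does not prescribe it. The percentages above are likewise a ceiling: recall at weeks 6 and 12, the central number and the research officer's resupply contacts with NRT users would all narrow the gap.

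It is also fair that AEs are not a listed outcome, that the analysis is descriptive, and that related serious events go to the DMEC individually. These points limit the consequence. A reader might further infer that safety follow-up ceases before week 26. What Table 2 omits is the scheduled checklist. The central number remains, as does monitoring to resolution of events that could become serious. Omitting a checklist well after the 8-week course can be a reasonable choice.

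None of this removes the mismatch after week 6. Nor is it detail that an article leaves to a fuller document, because the article itself states both schedules.

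**Conclusion.** The inconsistency holds. After week 6 the text calls for weekly checks with no stated end and Table 2 gives one check, at week 12, under either reading of its columns. The gap includes the last two weeks of the stated NRT course.

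Unequal ascertainment by arm is a conditional risk. Under the literal reading of Table 2 it is 8-9 scheduled checks against 2. In the illustration, recorded-AE probabilities are at most about 15-37% against 4-10%, resting on the assumed 2-5% weekly risk and no recall. Under the calendar-stage reading it is zero.

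The impact is moderate: no formal AE comparison is planned, but the DMEC's view of safety by arm and the design of the definitive trial both draw on these counts. The schedule should be corrected.

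**What to change.** Reconcile the Adverse events text with Table 2 into one AE schedule that:

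- has the same frequency and mode of contact in all four arms;
- is not tied to BISCA attendance or to BISCA sessions ending after lapses;
- covers the whole of the stated NRT course; and
- has a stated end.

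Change the Table 2 row and column sub-headers to match, so that the early marks visibly apply to arms 1 and 2 as well. As an option, add the checklist to the existing 26-week visit: the saliva-sampling paragraph under Data collection and follow-up procedure anticipates that some participants will still report NRT use there.

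The cost is a correction to the text, the table and the operating procedures. If the weekly frequency is kept, arms 1 and 2 will need weekly phone checks, which the Adverse events text already provides for. The optional 26-week checklist uses a visit that already takes place.
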